##### *Coping styles*

will be measured with the Children’s Response Style Questionnaire (CRSQ). This 25-item self-report questionnaire categorizes adolescents’ responses to negative emotions in three subscales: ruminative response, distracting response, and problem solving. Each item describes a possible response and is rated on a 4-point scale, ranging from ‘almost never’ to ‘almost always’. The CRSQ demonstrates moderate levels of internal consistency [35].

#### Secondary outcome measures

##### *Anxiety*

according to adolescents will be measured with the Dutch translation of the Spence Children’s Anxiety Scale (SCAS) [36]. The SCAS includes a self- and parent reported questionnaire, each containing 44-items describing anxiety symptoms on a 4-point scale, from 1 (never) to 4 (always). The scale offers excellent internal consistency, concurrent validity, and sufficient test-retest reliability in both child and adolescent samples [37, 38] Spence, 1998; Spence, Barett, & Turner, 2003).

##### *Behavioural problems*

will be assessed using the Strengths and Difficulties Questionnaire (SDQ) [39] for both parents and adolescents. The SDQ contains 25 items divided over 5 scales measuring emotional symptoms, conduct problems, hyperactivity/inattention, peer relationship problems, and prosocial behaviour. The SDQ is widely used and has good psychometric properties in the Dutch population [40].

##### *Responsiveness of group care workers*

will be assessed using the subscale responsiveness of the Dutch translation of the Prison Group Climate Inventory (PGCI). The subscale consists of 12 items rated on 5-point scales, ranging from 1 = ‘I do not agree’ to 5 = ‘I totally agree’. The overall PGCI-scale with 63 items demonstrates good validity and reliability [41].

### Statistical analyses

The expected effect size for this trial was Cohen’s d = .50. Although in a Dutch study on the effectiveness of OVK among youth with subclinical levels of depression (CDI score >15), the effect size of Cohen’s d = .7 was found [21], we chose a more conservative effect size, because slightly lower levels of depression are expected in our target group, and the effect size is known to be smaller if adolescents have lower baseline levels of depression [17]. An a priori power analysis using G*Power 3.1 [42], for a two-sample *t*-test with a one-sided significance level of 0.05 and equal sample sizes, revealed that a sample size of 102 (51 for each group) is required to obtain a power of .8. To accommodate for the clustering effect, we inflated the sample size with a factor of 1.49 following the suggestions of Campbell et al. [43]. Expecting a drop-out percentage of approximately 20 %, based on the number of adolescents that are expected to be dismissed during the program, the total sample size must be 182 (91 for each group).

All data will be analyzed in accordance with the intent-to-treat (ITT) principle but will also be analyzed separately for the completers only. For the ITT analysis, missing values due to loss of respondents or missing item scores will be handled through multiple imputation using the Markov Chain Monte Carlo method in the statistical package Mplus6 [44]. Missing values will be estimated with logistic regression for categorical variables and ordinary regression for continuous variables.

The hypotheses will be tested with mixed effects linear regression analyses in Mplus6. Because adolescents are nested within groups and groups are nested within locations, a three-level analysis is most appropriate to account for the non-independence of the data. However, this technique requires relatively large numbers of clusters (~25) and members in clusters (~25) [45]. With 3 locations, 20 clusters, and 8–10 members in each cluster, a multilevel analysis is not suited. To correct for the problem of the potential non-independence of the data for the clusters, the TYPE = COMPLEX procedure in Mplus will be used. This procedure corrects the standard errors of the parameter estimates for dependency. These standard errors are unbiased estimates and will be greater in comparison to the standard errors derived from individual level analysis. The effect of location will be tested by introducing dummy variables in the regression equation. We will check for possible baseline differences between the two conditions in background variables (e.g., age, sex, and ethnic background, cognitive capacities) and depressive symptoms. These variables will be entered as covariates in the regression equation.

To explore the mediating role of adolescents’ cognitive styles, coping styles, and therapeutic climate, mediation analyses will be performed using Mplus. The significance of indirect paths will be tested via bootstrap sampling. Moderating effects of age, gender, and treatment setting on the relation between depression and anxiety will be explored by entering the moderating variables as predictors for depression/anxiety. The moderation and mediation analyses will be done for the OVK and TAU conditions separately. Reporting of the results of the study will be in accordance with the CONSORT statement [46].

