**Fig. 1 Fig1:**
[figure not shown]
Study design

Randomization will be conducted by an independent statistician of the Radboud University Nijmegen and will take place on the level of the naturally existing treatment groups rather than on the level of individuals (clustered randomization). In the Netherlands, residential treatment groups usually comprise 8–10 adolescents that follow the same treatment program, live in the same building, and are usually taken care of by a permanent staff of nurses and social workers. The benefits of randomisation of natural groups are as follows: (1) it minimizes contamination among adolescents and staff; (2) it best reflects the natural situation in residential treatment settings, increasing the ecological validity of the study; (3) adolescents who will receive the intervention program know each other already and are used to undertake therapeutic activities together; and (4) staff members who will conduct the program already have a therapeutic relationship with the adolescents. Stratification on the cognitive level (MID versus non-MID) will be needed in order to ensure that the cognitive level is evenly distributed across the control and intervention conditions.

To test the effectiveness of the intervention, all adolescents and their parents will complete self-report questionnaires approximately one month before the start of the program and before adolescents know to which condition they are assigned (Baseline, T1), approximately one week before the start of the program (T2), immediately after the program (T3), and three months after the end of the program (T4). Adolescents in the control condition will complete the questionnaires at exactly the same time points. To make sure that all adolescents (MID and non-MID) understand the questionnaires, adolescents will be assisted in filling out the questionnaires by a trained research assistant that is blind to condition.

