### Participants and procedure

An a priori power analysis revealed that a sample of N = 182 would be necessary to obtain a power of .8. Three large institutes for residential treatment, including Pluryn De Hoenderloo Groep (youth care), Pluryn Jan Pieter Heije (care for youth with intellectual disability), and Karakter child and adolescent psychiatry (youth mental health care) will participate in this study. All treatment groups with adolescents between 12 and 16 years old, boys and girls, with a full-scale IQ of 50 or higher will be invited to participate. There are 20 treatment groups with 8–10 adolescents each that meet these criteria, of which are 8 youth care groups (Pluryn De Hoenderloo Groep), 8 groups for youth with MID (Pluryn Jan Pieter Heije), 2 mental health care groups, and 2 mental health care groups for youth with MID (Karakter child and youth psychiatry). Five groups (40–50 adolescents) include only boys, three groups (24–30 adolescents) include only girls, and twelve groups (96–120 adolescents) include both boys and girls. If the participants in the groups agree to participate, they will receive more information about the program and training, and the CDI-2 will be administered as a baseline assessment for depression (T1). Subsequently, groups will be randomly allocated to either one of both conditions. From the treatment groups selected, none of the adolescents will be excluded in order to avoid stigmatization and social exclusion. All parents will receive a letter with information regarding the goals and content of the study and will be asked permission for their child’s participation by passive informed consent. Since not all parents may understand written Dutch, given the expected social and ethnic characteristics of the sample, group care workers will ask the parents if they have understood the letter and if they have any questions. Parents and adolescents are free to withdraw themselves from the study at any time. Next, 2–3 permanent staff members of groups allocated to the intervention condition will receive a three-day training conducted by two experienced and licensed psychologists with broad expertise in cognitive behavioural therapy. Subsequently, T2 will be administered, and the training program will start.

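### The stated power of .8 rests on 100 individual-level degrees of freedom although only 20 groups are randomised; with cluster-level degrees of freedom it is about .78 with 152 analysed, and a separate drop-out slip brings it to about .77

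*Protocol article*

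**What the plan says.** The Statistical analyses section sets the effect size ("The expected effect size for this trial was Cohen’s d = .50") and runs a G*Power calculation "for a two-sample *t*-test with a one-sided significance level of 0.05 and equal sample sizes". This "revealed that a sample size of 102 (51 for each group) is required to obtain a power of .8". For clustering, "we inflated the sample size with a factor of 1.49". A last step allows for loss ("Expecting a drop-out percentage of approximately 20" per cent) and arrives at 182, or 91 per arm. Participants and procedure repeats the claim: "An a priori power analysis revealed that a sample of N = 182 would be necessary to obtain a power of .8".

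The Design section says that randomisation "will take place on the level of the naturally existing treatment groups rather than on the level of individuals". Participants and procedure counts 20 eligible groups of 8 to 10 adolescents, that is, 160 to 200 in all. When Statistical analyses chooses a model, it treats this as a constraint: "With 3 locations, 20 clusters, and 8–10 members in each cluster" is its reason for not fitting a multilevel model. It plans cluster-corrected standard errors (TYPE = COMPLEX in Mplus) instead, with location dummies and baseline covariates that include depressive symptoms. It names no degrees of freedom or reference distribution. It also does not give the intracluster correlation or group size behind 1.49.

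**The concern.** An inflation factor for clustering makes the variance of the difference between conditions larger. It does not change how many independent units are available to estimate that variance. Condition is constant within a group, so with 20 groups in two arms at most 20 − 2 = 18 degrees of freedom support the test. The power calculation uses 102 − 2 = 100. The number of groups is not an input to it, although the same section treats that number as too small for a multilevel model.

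The loss allowance has a separate problem. To have n analysed after losing 20%, one must enrol n/.8. Multiplying by 1.2 falls short.

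At stake is the accuracy of a figure that the protocol states twice for its primary hypothesis, and against which a null result would be read.

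**Working it through.** **Inputs from the protocol.** d = .50; one-sided alpha .05; equal arms; factor 1.49; loss 20%; N = 182; 20 groups of 8 to 10. **Assumed:** the factor is correct as stated, and the test statistic follows a t distribution with cluster-level degrees of freedom (df).

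**Formula.** Power = P(T > c). T is noncentral t with the given df, c is the one-sided 5% critical value, and the noncentrality is d·√(n_eff/4). The effective total is n_eff = number analysed / 1.49.

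**1. The plan's own figures.** With 51 per arm, n_eff = 102, the noncentrality is .5·√25.5 = 2.525, df = 100 and c = 1.660. Power is .806. With 50 per arm it is .799, so 51 per arm is indeed the smallest number that reaches .80. Then 102 × 1.49 = 152, and 152 × 1.2 = 182.4, stated as 182. All the stated figures reproduce.

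**2. Change only the degrees of freedom (152 analysed, n_eff = 102).**

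| df | critical value | power |
|---|---|---|
| 100 | 1.660 | .806 |
| 18 | 1.734 | .783 |

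The loss due to df is .806 − .783 = .023. Charging three further df for cognitive level and two location dummies (15 df, critical value 1.753) gives .777.

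**3. The loss allowance.** 152/.8 = 190, not 182. Losing 20% of 182 leaves 182 × .8 = 145.6 analysed, so n_eff = 145.6/1.49 = 97.7 if the factor stays at 1.49.

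| df | power with 145.6 analysed |
|---|---|
| 100 | .791 |
| 18 | .768 |
| 15 | .762 |

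Of the fall from .806 to .768, .015 comes from the loss allowance (.806 to .791) and .023 from df (.791 to .768). With 190 enrolled and 20% lost, 152 are analysed and power at 18 df is again .783.

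**4. If the factor falls as groups shrink.** After loss, the mean group size is 145.6/20 = 7.28. Suppose that 1.49 was set for m adolescents per group. The implied intracluster correlation is .49/(m − 1), and the factor after loss is 1 + 6.28 × that value. The protocol does not give m, so this is a range:

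| m assumed | implied ICC | factor after loss | power at 18 df |
|---|---|---|---|
| 7.6 (152/20) | .074 | 1.466 | .774 |
| 8 | .070 | 1.440 | .780 |
| 9 | .061 | 1.385 | .794 |
| 10 | .054 | 1.342 | .805 |

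**5. No loss at all.** With all 182 analysed and 1.49 kept, power at 18 df is .844. The .78 therefore belongs to 152 analysed. It is not the power of the 182 before loss.

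**The case against.** The strongest reply is that the effect is small. At 18 df the figure is .783 against a stated .8, a gap of 1.7 points, and the choice of d = .50 and an approximate drop-out rate are themselves uncertain. This stands, and it is why the point is minor.

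Second, the planned analysis adjusts for baseline covariates, including depressive symptoms, and the power calculation takes no credit for that. An assumed R² of .05 restores .80 at 18 df with 152 analysed (n_eff = 102/.95 = 107.4, power .801). An assumed R² of .10 does so at 15 df with 145.6 analysed (97.7/.9 = 108.6, power .800). This also stands. For the same reason the 15-df figures should not be the headline: they charge df for covariates without crediting the variance those covariates remove. Cognitive capacity may also be entered as an individual IQ score, which need not cost a group-level df.

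Third, the protocol names no reference distribution, and an analysis plan that is not shown may do so. If the estimate were referred to a normal distribution, nominal power would not fall (.811 at n_eff = 102). The cost would move to the type I error: about .059 one-sided instead of .05 if the statistic really follows t with 18 df. On these inputs the unadjusted design does not have both .8 power and a 5% level.

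A reader might infer that the small number of groups alone pulls power down to .76 or .77, or that the trial is seriously underpowered. The protocol supports neither. Part of the fall below .78 comes from the loss allowance, the after-loss figure depends on an unstated group size, and baseline adjustment could close the gap.

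**Conclusion.** The point holds as a minor correction to a stated number. The .8 uses individual-level degrees of freedom for a design that randomises 20 groups. With at most about 18 df, unadjusted power on the plan's own inputs is about .78 with 152 analysed, against .806 by the plan's method. A second, independent slip in the loss allowance (182 where 190 follows) lowers it to about .77 after a 20% loss with 1.49 held fixed. The range is about .77 to .80 if the factor was set for 7.6 to 10 per group and shrinks with the groups.

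These figures assume a test that holds its one-sided 5% level on cluster-level df, 1.49 correct as stated, and no credit for covariates. They do not show that the design or the planned sample is inadequate.

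**What to change.** Keep the sample size and the 20 groups. In Participants and procedure and in Statistical analyses:

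- Restate the unadjusted power with cluster-level degrees of freedom: about .78 with 152 analysed, and about .77 after a 20% loss from 182 with the factor held at 1.49.
- Give the number of groups per arm, and the intracluster correlation and group size behind 1.49, as inputs to the calculation. With these, the after-loss range narrows to one figure.
- Show the loss allowance as division by .8, and say that 182 falls short of the 190 this gives.
- Note that adjustment for baseline depressive symptoms may offset the shortfall, with the assumed R² stated if credit is taken.

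The cost is one recalculation and a slightly lower printed power. No adolescents, groups or data are added.

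### The 20% drop-out allowance was applied as ×1.2 instead of ÷0.8, so the stated total of 182 should be 190 on the plan's own inputs (a minor correction)

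*Protocol article*

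**What the plan says.** The Statistical analyses section of the protocol article gives every step of the calculation:

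- Effect size: "The expected effect size for this trial was Cohen’s d = .50".
- Test: a two-sample *t*-"test with a one-sided significance level of 0.05 and equal sample sizes".
- Size before adjustment: "a sample size of 102 (51 for each group) is required to obtain a power of .8".
- Clustering: "we inflated the sample size with a factor of 1.49".
- Loss: "Expecting a drop-out percentage of approximately 20" per cent, which the article links to adolescents being dismissed during the program.
- Result: "the total sample size must be 182 (91 for each group").

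Participants and procedure repeats the result, saying that a sample of 182 "would be necessary to obtain a power of .8". The Abstract also gives N = 182. The formula for the drop-out step is not printed.

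On supply, Participants and procedure says "There are 20 treatment groups with" 8–10 adolescents each that meet the criteria.

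**The concern.** If a fraction of those enrolled will be lost, the number to enrol is the number required divided by the fraction that stays. Multiplying by one plus the drop-out fraction always gives too small a figure, because the loss applies to the larger enrolled number and not to the number required. The printed 182 looks like the multiplied version.

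The total sample size and the power of .8 are headline figures of the protocol, and the article presents 182 as the number required for that power. If the drop-out step is wrong, the trial falls short of its own requirement whenever the expected loss occurs. Anyone reusing the calculation would carry the slip forward.

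**Working it through.** **Inputs**, all from Statistical analyses: d = .50; two-sample *t*-test, one-sided 5%, equal arms; target power .80; clustering factor 1.49; drop-out 20%.

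**Step 1. Size before adjustment.** The noncentral *t* calculation gives 50.15 per arm, rounded up to 51, so 102 in total. This reproduces the article. Power at 51 per arm is .806, so rounding up leaves a little slack.

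**Step 2. Clustering.** 102 × 1.49 = 151.98, so 152 adolescents are required at analysis.

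**Step 3. Drop-out.**

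| Formula | Calculation | Total |
|---|---|---|
| required × (1 + 0.20) | 151.98 × 1.2 | 182.4, matching the stated 182 |
| required / (1 − 0.20) | 151.98 / 0.8 | 189.98, so 190 (95 per arm) |

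Applying drop-out before clustering changes nothing: 102 × 1.2 × 1.49 = 182.4 and 102 / 0.8 × 1.49 = 190. Starting from the unrounded 100.3 gives 179.3 or 186.8, and neither is 182. Of the variants tried, only ×1.2 on the stated 102 gives the printed figure.

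**Step 4. What 182 delivers at 20% loss.**

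- Retained: 182 × 0.8 = 145.6, about 146 against 152 required.
- Effective size with 1.49 held fixed: 145.6 / 1.49 = 97.7, or 48.9 per arm.
- Power: .791.

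**Step 5. The loss that 182 covers.** 1 − 151.98/182 = .165, so about 16.5%. Power for 182 enrolled, by drop-out:

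| Drop-out | Retained | Power (one-sided) |
|---|---|---|
| 16.5% | 152.0 | .806 |
| 18% | 149.2 | .7995 |
| 20% | 145.6 | .791 |
| 22% | 142.0 | .782 |

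**Step 6. What 190 delivers.** 190 × 0.8 = 152 retained; 152 / 1.49 = 102.0 effective; power .806.

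**Step 7. Supply.** 20 × 8 = 160 and 20 × 10 = 200. A total of 182 needs an average of 182/20 = 9.1 per group, and 190 needs 190/20 = 9.5.

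**The case against.** The strongest reply is that almost nothing is lost. Power of .791 rounds to .79 against a stated .8. The article calls the 20% approximate, and at 18% loss power is .7995. This stands, and it is why the point is minor.

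The .791 may also be pessimistic, because the clustering factor is held fixed after drop-out. Suppose that 1.49 is 1 + (m − 1) × ICC with m = 8 to 10. The article does not say so; the implied ICC would be .054 to .070. Losing 20% within groups would then lower the factor to about 1.38. That gives an effective size of about 145.6 / 1.38 = 105.5 and power of about .82. Covariate adjustment for baseline depressive symptoms could also help: an assumed baseline–outcome correlation of .3 would lift .79 to about .82. Both arguments are fair, but they rest on values that the article does not give and that its own calculation does not use. They soften the consequence and leave the arithmetic as it is. Multiple imputation keeps every randomised adolescent in the dataset, but it recovers little information on a missing outcome, so it does not replace the allowance.

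A reader might infer the opposite, that the trial has much less power than claimed. For 182 enrolled and 20% lost, two-sided 5% power is .69, or .65 with 18 group-level degrees of freedom. The documents do not support laying this on the drop-out step. The one-sided level is declared openly and the hypothesis in Goals and hypotheses is directional. With the slip corrected to 190, two-sided power is still only about .71. The choice of test and the degrees of freedom (which take the one-sided figure from .79 to .77) are separate matters of design. The limited pool is separate too: both 182 and 190 lie within 160–200.

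**Conclusion.** The point holds as a minor arithmetic error. On the article's own inputs, 182 is the product of a ×1.2 step, and an allowance for 20% loss gives 190. The stated total is 8 adolescents short (4 per arm, 8/190 = 4.2%). At 20% loss it leaves about 146 of the 152 required.

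The effect on power is about 1.5 percentage points, from .806 to .791. This assumes d = .50, a one-sided 5% *t*-test with individual-level degrees of freedom, exactly 20% loss, and the factor 1.49 held fixed. Under the cluster-size assumption described above, the target would still be met. No estimand, analysis or decision rule is affected, and a null result would be read in much the same way at 79% as at 80% power. The two-sided and 18-degrees-of-freedom figures are optional context and not part of the error.

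**What to change.** Make the same correction in the Abstract, in Participants and procedure, and in Statistical analyses, by one of two routes:

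1. State the total as 102 × 1.49 / 0.8 = 190 (95 per arm). This lies inside the 160–200 adolescents in the 20 eligible groups, but only near the top of that range, at an average of 9.5 per group.
2. Keep 182 and say what it delivers: it covers a loss of about 16.5%, and at 20% loss one-sided power is about .79 with the clustering factor held at 1.49.

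The second route is the more practical if the groups cannot supply 190. In either case, print the drop-out formula so that the figure can be checked. The second route costs only rewording and a slightly less favourable power figure. The first asks for 8 more adolescents, if the groups can supply them.

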### Goals and hypotheses

The aim of the present study is threefold: (1) to test the effectiveness of OVK within the usual treatment program (OVK + TAU) in reducing symptoms of depression (primary outcome) compared to treatment as usual alone (TAU), (2) to identify mechanisms that can explain program effects (cognitive bias, coping skills), and (3) to test the effects of OVK on secondary outcomes (anxiety, behavioural problems, and therapeutic climate). It is hypothesized that OVK + TAU will be more effective in reducing symptoms of depression in youth than TAU alone, immediately after the program and at three months follow-up. Regarding the explanatory mechanisms, it is hypothesized that OVK + TAU will decrease negative cognitive biases and increase the adequate coping styles. Both of these constructs are expected to mediate the hypothesized effect of OVK on symptoms of depression. Concerning the secondary outcomes, the OVK program is expected to decrease anxiety, since the program contains cognitive and behavioural strategies that are hypothesized to be effective not only for depression, but also for anxiety (e.g., to recognize and challenge threatening interpretations of neutral events, to employ relaxation strategies [23]). A positive effect on behavioural problems is expected, because behavioural problems are believed to be mediated by deficits in internal impulse regulation and poor self-control [24]. If adolescents learn and adopt cognitive techniques to more adequately regulate their levels of anxiety, they will possess a higher level of self-control to regulate their behaviour, eventually leading to a decrease in problem behaviour. Lastly, the responsiveness of group care workers is hypothesized to increase more in the OVK + TAU group than in the TAU group alone. In the TAU+OVK condition, group care workers will be trained in therapeutic skills necessary to correctly implement the program, including listening skills, conversational skills, and techniques to increase group cohesion. These factors are hypothesized to increase the perceived responsiveness of group care workers.

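### The single covariate rule includes baseline depression but not the own baseline of anxiety, behavioural problems or responsiveness, which costs precision on the secondary outcomes

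*Protocol article*

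**What the plan says.** All statements are in the protocol article.

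- **Scope of the model** (Statistical analyses): "The hypotheses will be tested with mixed effects linear regression analyses in Mplus6". No separate model is given for the secondary outcomes.
- **Covariates** (same section): "We will check for possible baseline differences between the two conditions in background variables (e.g., age, sex, and ethnic background, cognitive capacities) and depressive symptoms", followed by "These variables will be entered as covariates in the regression equation". For sites: "The effect of location will be tested by introducing dummy variables in the regression equation".
- **Third aim** (Goals and hypotheses): this covers anxiety, behavioural problems and therapeutic climate. For the last, "the responsiveness of group care workers is hypothesized to increase more in the OVK + TAU group than in the TAU group alone".
- **Baseline collection** (Design): "all adolescents and their parents will complete self-report questionnaires approximately one month before the start of the program", before adolescents know their condition, and again at T2, T3 and T4. Instruments are not listed by time point.
- **Order of events** (Participants and procedure): at T1, "the CDI-2 will be administered as a baseline assessment for depression (T1"). Allocation comes next, then the three-day training of staff in the intervention groups. Then: "Subsequently, T2 will be administered, and the training program will start".

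**The concern.** The covariate rule suits the primary outcome, whose own baseline is on the list. For the other outcomes it adjusts for a different construct. The examples introduced by e.g. illustrate background variables (age, sex, ethnic background, cognitive capacities), and a baseline SCAS, SDQ or PGCI score is not naturally a background variable. The covariate that is usually most prognostic for each secondary outcome is therefore absent from the stated model.

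This matters more here than in a large individually randomised trial. Only 20 intact groups are allocated, with stratification on cognitive level alone. Responsiveness is a rating of a group's permanent staff, so it may well cluster strongly. A pre-existing difference between groups that happens to fall unevenly between arms would go uncorrected into the T3 and T4 contrasts, and variance that the baseline could explain stays in the error term.

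**Working it through.** **1. The plan's own figures.** For d = .50, one-sided .05 and a two-sample t-test, the noncentral t gives 51 per arm (power .806), matching the stated 102. Then 102 × 1.49 = 151.98, and 151.98 × 1.2 = 182.4, matching 182. These figures concern depression and do not depend on this point.

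**2. Inputs for the precision check.** Analysed sample: 182 × 0.8 = 145.6, taken as 146. Effective sample: 146 / 1.49 = 98. The d = .50 is stated for depression and borrowed here. All correlations are assumptions:

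- r1: baseline CDI-2 with the outcome
- r2: own baseline with the outcome
- r12: baseline CDI-2 with own baseline

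**3. Formulas.**

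- Residual variance with CDI-2 only: 1 − r1².
- Residual variance with own baseline added: 1 − (r1² + r2² − 2·r1·r2·r12) / (1 − r12²).
- SE² = (4/98) × residual variance. Power is from the noncentral t with 96 df, one-sided .05.

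Example, responsiveness (r1 = .1, r2 = .5, r12 = .2). CDI-2 only: 1 − .01 = .99. Both: 1 − (.01 + .25 − .02)/.96 = .75. Noncentrality rises from .5/√(.0408 × .99) = 2.49 to .5/√(.0408 × .75) = 2.86.

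| Outcome (r1, r2, r12) | Residual variance | SE ratio | Power at d = .50 |
|---|---|---|---|
| Responsiveness (.1, .5, .2) | .99 to .75 | .87 | .795 to .883 |
| SDQ (.2, .5, .3) | .96 to .747 | .88 | .806 to .884 |
| Anxiety (.3, .5, .5) | .91 to .747 | .91 | .824 to .885 |
| Anxiety, more overlap (.4, .5, .6) | .84 to .734 | .94 | .850 to .889 |
| Anxiety, strong overlap (.5, .5, .7) | .75 to .706 | .97 | .883 to .900 |
| Responsiveness, weak r2 (.1, .3, .2) | .99 to .908 | .96 | .795 to .825 |

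At d = .40 the first row goes from .63 to .73. The gains therefore run from about 2 to about 10 points for r2 between .3 and .5. With r2 of .6 to .7, other assumed sets (51 per arm, normal approximation) give SE ratios of 0.73 to 0.87 and gains of roughly 7 to 15 points at d = .50.

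**4. Is the hypothesis of a larger increase still tested?** In a simulation of 20 groups of 7 (assumed ICC .06, pre-post correlation .6, 3,000 runs, true effect 0.5), the post-score, change-score and baseline-adjusted estimators averaged 0.498, 0.500 and 0.499. With no effect they averaged 0.007, −0.002 and 0.002. All three estimate the same arm difference. With the true effect, the empirical SEs were 0.201, 0.179 and 0.162, so adjustment lowers the SE by 1 − 0.162/0.201 = 19% relative to the post score.

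**5. Size of chance imbalance.** With 10 v 10 groups of 9, the SD of the baseline arm difference is √[(2/10)(ICC + (1 − ICC)/9)]. The factor 1.49 implies ICC = .49/8 = .061.

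| ICC | SD of arm difference | P(gap above 0.3 SD, either direction) |
|---|---|---|
| .06 (implied) | 0.18 | 10% |
| .2 (assumed) | 0.24 | 21% |
| .3 (assumed) | 0.27 | 28% |

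These figures ignore stratification and the other covariates.

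**The case against.** **Validity.** A reader might infer that the hypothesis of a greater increase in responsiveness goes untested because post-programme levels, not increases, are compared. That does not follow. Under randomisation the arm difference in post scores and the arm difference in change have the same expectation, and step 4 of the working shows it. Omitting the baseline costs efficiency only.

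**Imbalance as bias.** A reader might also treat chance imbalance as an added bias. It is part of the sampling variance that the cluster-corrected standard errors are meant to carry, so it is the same precision loss seen from another side. Stratification on cognitive level, the location dummies and cognitive capacities as a covariate absorb some of it.

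**Form of the response.** The article does not say whether the response is a post score, a change score or repeated measures. Under the last two, the own baseline would already be used in some form and the loss would be smaller. This stands as a limit on the size of the point.

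**Baseline availability.** That SCAS, SDQ and PGCI are collected at T1 is not settled: Design speaks of questionnaires generally, while Participants and procedure names only the CDI-2. This also stands, and it makes the fix conditional on a T1 score.

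**Article brevity.** Covariates for each secondary outcome might sit in a full plan that is not shown. But the article does not leave covariates to another document. It states a rule and attaches it to an equation serving every hypothesis, and that rule fits the primary outcome only.

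**Conclusion.** The point holds as one of efficiency and clarity on the secondary outcomes. As written, anxiety, behavioural problems and responsiveness are not adjusted for their own baseline. The primary outcome and the sample size of 182 are unaffected.

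The power forgone is about 2 to 10 points for own-baseline correlations of .3 to .5, and more if the correlations are higher. It is smallest for anxiety if baseline depression already carries most of the information. The size rests on four assumptions: the correlations, an effect size borrowed from depression, the same design factor of 1.49 with and without adjustment, and a post-score response. Confidence is moderate, because the form of the response and the T1 instruments are not stated.

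**What to change.** In Statistical analyses, replace the covariate rule for the secondary outcomes with wording such as: each secondary outcome (SCAS, SDQ, PGCI responsiveness; adolescent and parent versions separately where both exist) is analysed with its own T1 score from the same informant as a prespecified covariate, regardless of observed imbalance, in addition to the other covariates.

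Two accompanying clarifications are needed:

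- Reconcile Design with Participants and procedure on which instruments are given at T1. Where an outcome has no T1 score, say so for that outcome.
- Do not use T2 as the responsiveness baseline. By then the intervention groups' staff have been trained in listening and conversational skills that the article expects to raise responsiveness, so adjusting for T2 could remove part of the effect under study.

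The cost is a few sentences and one degree of freedom per model. If the T1 scores exist, no new data, visits or participants are needed.
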